### Outcome Measures

The primary outcome assessed will be the changes in participant food insecurity score (evaluated by the HFIS) from baseline to 3 months. Secondary outcomes at 3 months will be changes in dietary habits (evaluated by 2-day 24-hour recall, PREDIMED index [31], and food frequency questions), changes in indicators of nutritional status (body mass index [BMI] and albumin and prealbumin levels), changes in muscle strength improvement (evaluated by dynamometer), changes in quality of life (EQ-5D-3L) [33], changes in fatigue scale (FACIT-F) [34], changes in serological markers of cardiovascular risk (insulin resistance, cholesterol levels, hemoglobin A_1c_, high sensitivity C-reactive protein, adipocytokines, interleukin 1, interleukin 6, and tumor necrosis factor), changes in physical activity (EMS [32] and IPAQ [35]); changes in body composition balance evaluated by bioimpedance, changes in inpatient admissions and outpatient appointments, changes in falls, and changes in knowledge regarding healthy lifestyle.

The secondary outcomes at 6 months will be changes in participant food insecurity score, changes in dietary habits (2-day 24-hour recall, PREDIMED index [31], and food frequency questions), changes in quality of life (EQ-5D-3L) [33], changes in fatigue scale (FACIT-F), changes in physical activity (IPAQ) [35], changes in inpatient admissions and outpatient appointments, changes in falls, and changes in knowledge regarding healthy lifestyle.

### Sample Size

Sample size was estimated considering a *t* test (independent samples) for comparing the mean change in food insecurity score from baseline to the end of study between group 1 (intervention) and group 2 (control). The intervention is considered to be meaningful if 50% of the individuals in group 1 have a decrease of 1 point in the food insecurity score, all the remaining being unchanged. This results in a difference of –0.5 between the mean changes of the 2 groups. Standard deviation of the change is assumed to be 1.5. Power is set at 0.80 and α=.05. We expect to include and randomize 141 experimental and 141 control elderly people with food insecurity (n=282) equally distributed among the 17 primary care centers. We are prepared to recruit around 70 individuals in each primary care center (a total of 1128 subjects are needed) because we assume that 50% (based on the INFOFAMÍLIA [National Survey on Food Insecurity in Portugal] survey) [36] of the target individuals are food insecure and that 50% of those will adhere to the study.

Of note, the standard approach to sample size calculation based on a clinically important difference was not possible to use in this study because data on interventions in food insecurity are scarce. We have considered the referred effect size based on the INFOFAMÍLIA survey data. In this study, the majority of Portuguese food-insecure households are in low food insecurity level (39.8%), and about 80% of those in the low food insecurity level obtained just 1 point in the food insecurity score, which means that if our intervention decreases the food insecurity score by 1 point we will be able to see a change from the low food insecurity level to the food security level.

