A nutrition and physiotherapy assessment will be performed at baseline and end of intervention assessment (at 3 months). The nutritionist will collect data regarding food insecurity (Household Food Insecurity Scale [HFIS] adapted from the US Department of Agriculture Household Food Security Survey Module [21]), dietary habits (2-day 24-hour diet recall, Prevención con Dieta Mediterránea [PREDIMED] index [31], and food frequency questions), anthropometric data (height, weight, and waist circumference), body composition data obtained by bioimpedance (fat mass, fat-free mass, total body water), attitudes and barriers on diet, food expenses, and other resources for food. Regarding the dietary habits assessment, a second 24-hour diet recall will be performed by phone call interview performed within 1 week.

Physiotherapy assessment will be conducted aiming at collect data regarding physical activity (Elderly Mobility Scale [EMS] [32] and International Physical Activity Questionnaire [IPAQ]) and muscle strength (hand grip, knee extension, and hip flexion by using a dynamometer). The assessment scales used in the study are all Portuguese-validated versions, and the average time for the evaluation will be 90 minutes.

The nurse will perform a structured questionnaire in order to capture baseline knowledge on healthy lifestyles. This questionnaire will be repeated during the 3-month and 6-month follow-up assessments.

Blood samples will also be collected in order to obtain data regarding the nutritional status and serological biomarkers of cardiovascular risk (albumin and prealbumin levels, insulin resistance, cholesterol levels, hemoglobin A_1c_, adipocytokines, high sensitivity C-reactive protein, interleukin 1, interleukin 6, and tumor necrosis factor).

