### Data Analysis

Analysis will be performed with Stata software (StataCorp LLC). Continuous variables will be reported as mean and standard deviation (or in case of nonnormal distribution as median and interquartile range). Categorical variables will be displayed as frequencies or proportions. The association between food security status, dietary data, and health outcomes will be assessed through chi-square analysis of baseline data.

To assess the effect of the interventional program on food security, dietary intake, nutritional status and body composition, quality of life, muscle strength, fatigue scale, physical activity habits, and serological markers of cardiovascular risk, 2-tailed *t* tests will be used to compare the amount of change within each group (baseline, end of study [at 3 months] and follow-up [at 6 months]). Independent sample *t* tests will be used to compare the intervention group and control group on the same outcomes.

Dietary intake assessed with 2-day 24-hour recall will be analyzed according to the recommended number of servings from each food group of the Portuguese Food Wheel [37]. Intakes of micronutrients that tend to be low in vulnerable population groups (iron, calcium, folate, and vitamins A, C, and D) will be also analyzed. The percentage of individuals meeting the Estimated Average Requirement or Adequate Intake for iron, calcium, folate, and vitamins A, C, and D will be calculated [38]. Food Processor Nutrition Analysis software (ESHA Research) will be used to estimate the intakes of energy, macro-, and micronutrients.

The association between each outcome and the candidate covariables will be performed using generalized models. We will use multivariate logistic and linear (according to the outcome) regression models. The candidate covariates will be first analyzed by univariate regression. Covariates will enter the multivariate models if their *P* value is less than .25 in univariate analysis or considered clinically relevant in this setting. The selection of covariates will be stepwise by backward selection, according to the level of significance (<.05). Multilevel analysis and sensitive analysis will be performed when appropriate.

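### The 80% power is quoted for the 282 randomised, but 141 per arm is the bare complete-data t-test number, with no allowance for loss before the 3-month HFIS

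*Protocol article*

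**What the plan says.** In the protocol article, Outcome Measures defines the endpoint: "The primary outcome assessed will be the changes in participant food insecurity score (evaluated by the HFIS) from baseline to 3 months". Sample Size bases the calculation on an independent-samples t test "for comparing the mean change in food insecurity score from baseline to the end of study between group 1 (intervention) and group 2 (control"; Data Analysis equates end of study with 3 months, so the two sections agree on the time point.

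The inputs in Sample Size are explicit:

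- Effect: "This results in a difference of –0.5 between the mean changes of the 2 groups".
- Variability: "Standard deviation of the change is assumed to be 1.5".
- Error rates: "Power is set at 0.80 and α=.05".
- Number randomised: "We expect to include and randomize 141 experimental and 141 control elderly people with food insecurity (n=282".

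The same section then works back to recruitment. It takes 1128 people as needed, assumes that half are food insecure, and assumes that half of those will adhere to the study. The Abstract gives the same chain and attaches the figure 282 to the adherence step.

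Under Data Collection, the 3-month assessment takes place at the primary care centre with a four-discipline team, and "the average time for the evaluation will be 90 minutes". Only the 6-month assessment is by telephone. Ethical Considerations states that participants may withdraw at any time.

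**The concern.** A change-score t test uses only participants with both a baseline and a 3-month score. If the number randomised equals the number the formula needs, the quoted power assumes that nobody is lost in between. The population is food-insecure people aged 60 and over who must return to a clinic for the primary outcome, so some loss is foreseeable.

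At stake is the accuracy of a design figure that funders, ethics committees and readers rely on. If loss is appreciable, the chance of missing the 0.5-point difference that the protocol calls meaningful is larger than the 20% it implies. At 20% loss it is about 30%.

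**Working it through.** **Inputs.** From Sample Size: difference 0.5, SD of change 1.5, power 0.80, α 0.05, 141 per arm. From Randomization, Allocation, and Blinding: 1:1 allocation. Sidedness is not stated in Sample Size. Data Analysis says "2-tailed *t* tests will be used to compare the amount of change within each group", and only a two-sided calculation gives about 141 (one-sided gives 112), so two-sided is used here. Loss rates are assumptions, because the documents give none.

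**Step 1: reproduce the plan's figure.**

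n per arm = 2 × (1.96 + 0.8416)² × (1.5/0.5)² = 2 × 7.849 × 9 = 141.3.

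The noncentral-t solution is 142.2, so 143. The stated 141 matches the normal formula with complete data and contains no margin. Power at 141 per arm is 79.9% by the normal approximation and 79.7% by exact t.

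**Step 2: locate the two 50% allowances.**

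1128 × 0.5 × 0.5 = 282.

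The product equals the number randomised, so both factors are used up before randomisation. Had the second one described retention afterwards, 1128 × 0.5 = 564 would be randomised, and the article says 282.

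**Step 3: power after loss d, equal in both arms.** Number analysed per arm = 141 × (1 − d), with difference 0.5 and SD 1.5 unchanged.

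| Assumed loss | Analysed per arm | Power, normal | Power, exact t |
|---|---|---|---|
| 0% | 141 | 79.9% | 79.7% |
| 5% | 134 | 77.9% | 77.6% |
| 10% | 127 | 75.7% | 75.3% |
| 15% | 120 | 73.3% | 72.9% |
| 20% | 113 | 70.7% | 70.3% |
| 30% | 99 | 64.9% | 64.4% |

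**Step 4: the same loss as a detectable difference.** At 20% loss, 141 × 0.8 = 112.8 per arm. The difference detectable with 80% power is 2.8016 × 1.5 × √(2/112.8) = 0.56, against the planned 0.50.

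**Step 5: what a baseline-adjusted analysis would give.** Assume equal variances at the two times and correlation ρ between baseline and 3-month HFIS. The change-score variance is 2σ²(1 − ρ) = 2.25 and the ANCOVA residual variance is σ²(1 − ρ²), which equals 2.25 × (1 + ρ)/2.

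- ρ = 0.5: variance 1.69, SD 1.30. With 15% loss (119.85 per arm), power is about 84%.
- ρ = 0.7: variance 1.91, SD 1.38. With 15% loss, power is about 80%.

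With the change SD held at 1.5, the gain shrinks as ρ rises; at ρ = 0.8 power is about 77%.

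**The case against.** **Nothing is miscalculated.** This stands. The formula gives 141.3 and the recruitment product is exact. The point concerns an unstated planning assumption about retention. A reader might infer an arithmetic error in the 282, and there is none.

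**The article is condensed, so a retention allowance may sit in the full protocol.** This has limited force. Sample Size gives all its inputs and names two allowances, so a third would be expected beside them. The stated number also reproduces with no inflation.

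**The word *adhere* may mean retention.** Step 2 rules this out.

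**Around 70 per centre gives slack.** 70 × 17 = 1190, which would yield about 297 randomised and, at 5% loss, about 141 per arm analysed. But the article states the need as 1128 and fixes randomisation at 282, so this is rounding and not a declared margin.

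**The SD is just as soft.** This is fair. The 1.5 is an assumption without a cited source. The protocol's own scenario (half fall by 1 point, all others unchanged) implies an SD of 0.5 in the intervention arm and 0 in control. A true SD of about 1.42 would restore 80% power at 10% loss, and about 1.33 at 20%. The true SD could equally be larger, and a cautious SD is not a stated loss allowance.

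**No loss rate is documented.** This also stands. A reader might infer that 80% power is out of reach under any realistic retention. The documents do not support that: at 5% loss the cost is about 2 percentage points. The 90-minute visit makes some loss plausible but says nothing about its rate, since participants will already have been through the baseline assessment.

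**Conclusion.** The concern holds in a limited form. The protocol pairs 80% power with 282 randomised, and that pairing is right only with essentially complete 3-month HFIS scores. Both stated allowances apply before randomisation and none applies after it.

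The size depends on retention, which the documents leave open: about 2 points of power at 5% loss, 4 at 10%, 9 at 20% and 15 at 30%. It is negligible with excellent follow-up and material from about 10%. These figures assume equal loss in both arms, loss that leaves the difference of 0.5 and the SD of 1.5 unchanged, and the unadjusted t test on change.

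A reader might also infer that enrolment has to rise. That does not follow. What needs correcting is the statement of power, which should be made because the figure is relied on and the correction is cheap.

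**What to change.** **Main change, one paragraph in Sample Size.** State the assumed 3-month retention with its basis, and give the power for the number expected to be analysed. For example: *With 141 randomised per arm and an assumed 10% loss by 3 months, about 127 per arm will be analysed, giving about 75% power for a difference of 0.5 (about 70% at 20% loss).* The detectable difference can be given instead, for example 0.56 with 80% power at 20% loss. It would also help to say that both 50% allowances apply before randomisation. No increase in enrolment is required. The only cost is a less favourable stated power.

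**Separate option, a change of analysis.** The primary comparison could be pre-specified as ANCOVA of the 3-month HFIS on the baseline HFIS, which is already collected. This is more than a restatement. Data Analysis specifies independent-sample t tests, and its regression models choose covariates by P value, so baseline HFIS would have to be fixed in the primary model in advance. Under the assumptions of Step 5, it would give about 84% power at 15% loss if the baseline/3-month correlation is 0.5, and about 80% if it is 0.7. The documents give no correlation, so it must be stated as an assumption. The cost is an amendment to the primary analysis, settled before outcome data are seen by arm.

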### Randomization, Allocation, and Blinding

Randomization will be computer generated. Randomization will be stratified according to gender and food insecurity level (low/moderate vs severe) with permuted blocks of six. Subjects will be allocated to the study group versus control with a probability of 1:1.

We will ensure researchers taking follow-up outcome measures will be blinded to group allocation; after randomization, the intervention group will be informed that they will have access to the intervention program (TV app) by an independent assessor (single-blind).

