### Study Population and Recruitment Plan

A convenience sample of food-insecure elderly people from 17 primary care centers of *Lisboa e Vale do Tejo* health region will be enrolled in this study. All elderly subjects who attend health services in the selected primary care centers during the recruitment period will be approached by our research team and asked to complete a questionnaire for the initial screening. The questionnaire includes a food insecurity scale to identify food-insecure elderly persons, and an authorization request form will be provided to obtain consent for a further contact. All elderly subjects identified as food insecure will be invited to participate in this study. The baseline assessment will be performed during an appointment at the primary care center with a multidisciplinary team that includes a medical doctor, nurse, nutritionist, and physiotherapist. The medical doctor will ask for informed consent and check inclusion and exclusion criteria.

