### Eligibility

To be eligible for this randomized controlled study, subjects must fulfill all of the following inclusion criteria: (1) aged 60 years or older, (2) identified as food insecure in the recruitment [21], (3) able and willing to give written informed consent and phone number contact and comply with other requirements of the study protocol, (4) Portuguese speaker or able to understand Portuguese, (5) noninstitutionalized and living in a private household in Portugal, (6) have electricity at home, and (7) have cable TV with box at home. The exclusion criteria are as follows: (1) inability to comply with study protocol (hearing/visual loss, cognitive impairment, etc); (2) absolute contraindication to exercise; (3) have cable TV operated by other companies than MEO, Vodafone, or NOS; and (4) have a household member involved in this study.

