### Description of the Intervention

Our intervention program is based on a cognitive behavioral strategy for promoting lifestyle behavior changes, combining sets of different strategies that will be important to the learning process as well as to behavioral changes.

This tool was developed based on the transtheoretical model [22] that conceptualizes the process of intentional behavior change in 5 stages, from precontemplation to maintenance. This intervention program accompanies the participants through all these phases. At T0 clinical appointments, doctors, nutritionists, physiotherapists, and nurses lead the participant through the stages of precontemplation and contemplation. In the preparation and action phases—when the subject intends to change behaviors and in fact does change them—the intervention program offers them all the cognitive and behavioral tools to achieve the changes. In addition, the intervention promotes helping relationships, since participants have at their disposal the telephone number and the possibility to contact the team as regularly and as often as they wish. The program also considers the phases of maintenance and prevention of relapse in the T1 clinical appointment and 3 months after the program.

The contents of the intervention program using a TV app were developed closely regarding Kolb’s experiential learning model [23,24]: videos on physical exercise and recipes (reflective and active experimentation); videos with tips on nutrition and healthy lifestyles (abstract conceptualization); queries; reminders; and the option to contact the medical doctor, nutritionist, nurse, and physiotherapist.

We designed an interventional program using an interactive TV app to improve dietary habits and physical activity levels among elderly populations with food insecurity. Of the several ICTs available, we have chosen the TV app because the majority of elderly people with food insecurity watch TV [25]. Unpublished data from our group have shown that TV is the most important source of health information for this group.

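### A single published block size of six lets someone who sees a stratum's whole sequence be certain of up to about a quarter of assignments; undisclosed varying sizes would be a cheap improvement

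*Protocol article*

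**What the plan says.** All references are to the protocol article.

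- **Randomization, Allocation, and Blinding.** The scheme is computer generated: "Randomization will be stratified according to gender and food insecurity level (low/moderate vs severe) with permuted blocks of six". The ratio is equal: "Subjects will be allocated to the study group versus control with a probability of 1:1". This makes four strata (two by two); centre is not one of them.
- **Same section, blinding.** "We will ensure researchers taking follow-up outcome measures will be blinded to group allocation". After randomization an independent assessor tells the intervention group about its access to the TV app. The trial is labelled single-blind.
- **Study Population and Recruitment Plan.** A food insecurity scale is completed at screening. At the later baseline appointment, "The medical doctor will ask for informed consent and check inclusion and exclusion criteria".
- **Eligibility.** One exclusion is open-ended: "inability to comply with study protocol (hearing/visual loss, cognitive impairment, etc").
- **Data Collection.** The doctor's evaluation comes first, and the nutritionist then collects the HFIS. The clinic assessments are done by doctor, nurse, nutritionist and physiotherapist.
- **Description of the Intervention.** Participants have a telephone number for contacting the team as often as they like, and the program includes "the option to contact the medical doctor, nutritionist, nurse, and physiotherapist".
- **Outcome Measures.** The primary outcome is the change in HFIS score from baseline to 3 months.

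**The concern.** With a fixed and known block of six at 1:1, each block holds three places per arm. Once one arm's three places are used, every remaining assignment in that block is determined. Anyone who has followed the stratum and knows where the block began then knows the next arm.

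The professions that run the baseline visit have an open channel to participants who know their arm, so earlier assignments could reach them. The eligibility decision leaves room for judgement, and the baseline HFIS is taken by an interviewer. The stated blinding is for those who take follow-up measures. A predicted assignment could therefore influence who is enrolled or how the baseline score is recorded. An error in the baseline score passes point for point into the change score, and blinding at 3 months would not remove it.

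**Working it through.** **Inputs from the article.** Block size 6; ratio 1:1; four strata; 17 centres; 282 participants, 141 per arm; target difference 0.5 points; SD of change 1.5; power 0.80; alpha 0.05, taken as two-sided.

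**The plan's own figure.** The article gives no figure for predictability. Its sample size reproduces: 2 × (1.960 + 0.842)² × 1.5² / 0.5² = 141.3 per arm, against 141 stated; power at 141 is 0.80.

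**Certain assignments in one block.** There are C(6,3) = 20 equally likely orders.
- 4th place is forced if the first three are alike: 2/20 = 10%.
- 5th place is forced if the first four split 3 to 1: 8/20 = 40%.
- 6th place is always forced: 100%.
- Expected number: 0.1 + 0.4 + 1.0 = 1.5 of 6, or 25%. The closed form for block size 2b is 1/(b + 1) = 1/4.

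**Best guess.** Always naming the arm with more places left gives 3 + (2⁶/20 − 1)/2 = 4.1 correct of 6, or 68.3%, against 50% by chance.

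**Over the whole trial.** Incomplete last blocks lower the certain share slightly. Simulation gives about 24%. So 0.238 × 282 ≈ 67, up to 0.25 × 282 ≈ 70.

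**By what the observer knows.** These are simulated with 282 participants and 17 centres. Assumptions not in the article: half are women, and the severe share is 10%, 25% or 50%.

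| Knowledge | Certain assignments |
|---|---|
| Whole stratum sequence, all centres | about 24% |
| Own centre only, one list per stratum (as the article reads) | about 0.005% or less |
| Own centre, with a separate list per centre (not stated; 68 cells, about 4.1 participants each) | about 11% to 17% |

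**Effect of varying sizes.** This is simulated for an observer who sees the whole stratum and knows the set of sizes, but not their order.

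| Block sizes | Certain | Best guess correct |
|---|---|---|
| 6 | about 24% | about 68% |
| 4, 6 and 8 at random | about 2% | about 67% to 68% |

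**Illustration of bias (assumed shift, whole-stratum observer).** If each certain prediction shifts the HFIS change by d in the favoured direction in each arm, the bias is 2 × 0.25 × d = 0.5d. The standard error is 1.5 × √(2/141) = 0.179.
- d = 0.1: bias 0.05; the test rejects about 5.9% of the time under no effect.
- d = 0.2: bias 0.10, which is 20% of the 0.5-point target; rejection about 8.6%.
- d = 0.2 with every best guess acted on: bias 2 × (2 × 0.683 − 1) × 0.2 ≈ 0.15; rejection about 12.9%.

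No value of d can be taken from the article. For an observer with own-centre knowledge only, the bias from certain predictions is close to zero and rejection stays near 5%.

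**The case against.** The strongest case against is that the quarter needs an observer whom the article does not describe. Centre is not a stratum, so certainty requires the ordered history and block boundaries of a stratum across 17 centres. Occasional telephone contacts would not supply that. This stands, and it is why 25% can only be an upper bound. Near-zero is not established either. The article speaks of one research team and a multidisciplinary team working at the centres, and does not say that each centre has its own staff. A team that works across centres would move towards the higher figure.

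A reader might infer that the trial is open and that nothing shields enrolment or the baseline score. The text does not support that. It says single-blind, blinds those who take follow-up measures, and has an independent assessor tell the intervention group. The same professions do the 3-month clinic assessments, so if that blinding holds they should not know earlier assignments. The contact option is a plausible leak, not a stated one.

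A reader might also infer that assignments are predictable before the baseline HFIS is taken. That holds only if the screening scale sets the stratum. If the baseline HFIS sets it, the stratum is not fixed until that score exists. The article does not say which.

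Finally, varying the block size leaves best-guess accuracy almost unchanged, so much of the protection lies in concealment. This is correct. But who holds the list and when an assignment is released are details that an article may leave to the full protocol, so their absence is not counted here.

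**Conclusion.** The point holds as a cheap improvement to a stated design choice. It is not an error or a contradiction. Fixing and publishing one block size makes about 24% to 25% of assignments certain for someone who knows a stratum's complete sequence, and almost none for staff limited to their own centre under one list per stratum.

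The upper figure rests on three conditions: earlier assignments become known across centres, block boundaries can be tracked, and, for any effect on the baseline HFIS, the stratum is already known from screening. The article establishes none of these. Its contact arrangements make the first plausible.

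The bias and rejection figures are illustrative only. A reader should not conclude that the trial's type I error is 8.6% or that its result would be biased by 0.10 points.

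**What to change.** In Randomization, Allocation, and Blinding, replace the fixed block of six with permuted blocks of randomly varying size (for example 4, 6 and 8), with the sizes not disclosed to recruiting or assessing staff. Keep the computer-generated system, the 1:1 ratio and the two stratification factors.

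Optional supporting wording, if the full protocol does not already have it: the list is held outside the recruiting and assessing team, and an assignment is released only after eligibility is confirmed and the baseline HFIS is locked. This would address the guessing that varying sizes leave in place.

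**Cost.** One setting in the randomization program and a short change of text, before recruitment begins (planned for the end of 2017). The largest end-of-stratum imbalance rises from 3 (half of 6) to 4 (half of 8). No extra participants, staff or visits are needed.
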